## 7 STUDY DESIGN

The current study design, a multi-arm adaptive platform trial, was chosen to adjust to the very dynamic circumstances of the SARS-CoV-2 pandemic. Furthermore, its design, but also the choice of endpoints, was based on the master protocol published by the World Health Organization (74). Numerous trials are currently being conducted and new information, both on trial results and on potential new experimental treatments, are being published on a daily basis. In this context, the choice of an adaptive, multi-arm platform design seems most suitable to be able to rapidly adjust to new circumstances. Some of the treatment arms may only be opened when the respective product and all necessary documentation becomes available (e.g. IVIgG). A new treatment arm will only be opened after submission of a substantial amendment. Moreover, new treatment arms may be added later and other treatment arms may be closed, if proven futile or even harmful (always with notification/submission of substantial amendments to the ethics committee or competent authorities). Since there is no established treatment for COVID-19 inclusion of a SOC arm seems justified and allows another dimension of comparison. While the SOC may differ between hospitals, it may include currently available, approved treatments for COVID-19, e.g. remdesivir and/or dexamethasone, but may also include other treatments which have been used well before remdesivir has become available. If remdesivir is not part of SOC, then patients may be randomized to receive remdesivir vs. SOC. However, since remdesivir is the only approved treatment of COVID-19, treating physicians may still decide to use remdesivir, if the clinical situation requires it. Sub-study A will only be available to patients without therapeutic anticoagulation. Sub-study B will only be opened for patients with a blood pressure >130/85 mmHg. In these patients, treatment with the lowest possible dose of candesartan is considered safe. The required dose will be titrated to normotension and may therefore be increased. However, in- and outpatients may be recruited. Two control groups will be included: Control group 1: In- and outpatients with suspicion of COVID-19, but with negative test results and control group 2: healthy volunteers with negative oral/nasopharyngeal swabs for SARS-COV-2. Sub-study C, designed to investigate immune-modulatory treatments/anti-inflammatory treatments vs. standard care ( $\pm$ placebo) will only be opened for patients with pneumonia, oxygen demand and incipient or established acute respiratory distress syndrome (in detail in in- and exclusion criteria). Patients may be included in the “main trial” or in sub-studies only. Patients may also only participate in one or more sub-studies or in the “main” antiviral part of the trial. Thus, one patient may also be eligible to more than one treatment arm.

There is no established, effective treatment for SARS-CoV-2 (or the disease SARS-CoViD-19). The aim of this trial is to answer several questions as rapidly as possible and to provide potentially beneficial treatment to these patients, always based on current knowledge and scientific data. Due to multiple arms with drugs of different sizes and formulation it will be impossible to blind the trial except for sub-study C.

**Patients may be eligible for sub-studies even if they do not fulfill criteria for antiviral therapy.**

[figure not shown]

Figure 1. flow-chart of the platform trial

Patients randomized to antiviral treatments are also eligible for the sub-studies. In contrast to other treatment arms and sub-studies, sub-study B may include in- and outpatients. For Sub-study B two further control groups will be included: control group 1: in- and outpatients with a suspicion of COVID-19, but who tested negatively for COVID-19 (n=10) and control group 2: healthy volunteers (n=10) will be included as another control group. Control group 1 will be recruited at the Departments of emergency medicine and the Department infectiology at the Medical University of Vienna. Control group 2 will be recruited at the Department of Nephrology, in collaboration with the Department of clinical pharmacology.

Sub-study C: depending on available medication in the respective trial centers, randomization to one of the substances will be possible.

Treatment arm 1 is inactive due to international reports on safety issues for (hydroxy-)chloroquine.

## 7.1 Study population

### 7.1.1 Subject population

The study population of the main study will consist of approximately 500 patients with a laboratory- or radiologically proven (i.e. PCR-based assay) infection with SARS-CoV-2. For those patients who have clear radiological signs of COVID-19, but a negative PCR result, repetitive PCR tests and an antibody-based

assays are required. The sub-studies A and B also aim to include 100 patients, while the initially planned sample sizes for sub-study C are  $n=300$  (3 different doses for 100 patients each) plus 100 control patients for asunercept and  $n=20$  for pentaglobin (plus 20 controls). Patients of the main study may participate in different sub-studies, thus treatment arms are not mutually exclusive. Treatments within one sub-study (or within the main trial) are mutually exclusive. For instance, within sub-study C patients may only be randomized to one treatment. Patients may also only participate in sub-studies, but not in the main trial (e.g. sub-study C). All patients in the study are diagnosed with COVID-19 except for the two control groups of sub-study B. For “antiviral” treatment arms only hospitalized patients will be able to participate, for sub-study A only patients without chronic anticoagulation are eligible, for sub-study B only patients with blood pressure  $>130/85\text{mmHg}$  in two repetitive measurements will be included. Noteworthy, only sub-study B may also include outpatients. Sub-study B may include two control groups: patients with suspicion of and negative test results for COVID-19 (Control Group 1) and healthy volunteers with negative test for COVID-19 (Control Group 2). Control group 1 will be recruited at the Departments of emergency medicine and the Department infectiology at the Medical University of Vienna. Control group 2 will be recruited at the Department of Nephrology, in collaboration with the Department of clinical pharmacology. For sub-study C, patients showing signs of respiratory deterioration will be included.

### 7.1.2 Inclusion criteria

- Laboratory confirmed (i.e. PCR-based assay) infection with SARS-CoV-2 (ideally but not necessarily  $\leq 72$  hours before randomization for “antiviral” treatments) OR radiological signs of COVID-19 in chest X-ray or computed tomography
- Hospitalisation due to SARS-CoV-2 infection, except for sub-study B, which may also include outpatients with COVID-19
- Requirement of oxygen support (due to oxygen saturation  $<94\%$  on ambient air or  $>3\%$  drop in case of chronic obstructive lung disease)
- Informed Consent obtained, the patient understands and agrees to comply with the planned study procedures, except for sub-study C: obtaining informed consent may be impossible due to the severe condition of the patient and may be waived
- $\geq 18$  years of age
- Sub-study A: not on chronic anticoagulation
- Sub-study B: Sub-study B: blood pressure  $\geq 130/85\text{mmHg}$  in 2 consecutive measurements OR patients with established and treated hypertension
- Sub-study B: Control group 1: Patients with suspicion of but negative tests for COVID-19. This group may consist of hospitalized and non-hospitalized patients.
- Sub-study B: healthy volunteers
- Sub-study C: Signs of respiratory deterioration and progressing inflammation: need for oxygen supplementation, non-invasive ventilation, high-flow oxygen devices or mechanical ventilation AND CRP levels  $>5\text{mg/dL}$  (for Pentaglobin only) and ICU admission (for Pentaglobin only)
- For female patients with childbearing potential: willingness to perform effective measures of contraception during the study.

### 7.1.4 Females of childbearing potential

Females of childbearing potential may participate in this clinical trial, although a negative pregnancy test is required during screening. Moreover, for the duration of the trial, negative pregnancy tests are required at least once a month. However, after evaluation of day 29 status (hospitalization, clinical performance etc.) the study ends for each participating patient. Thus, a pregnancy test during the screening visit should be sufficient.

Females of childbearing potential may not participate in the asunercept part of the study.

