### 7.1.5 Study duration

The clinical status of all patients will be evaluated on day 29. Thereafter, the trial ends for the individual patient randomized to antiviral treatment arms. The study ends after full recovery (or death) for patients in sub-studies B and C.

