#### **Sub-Study B: RAS blockade**

Initial dose: candesartan 8 mg 1-0-0; (compared to standard of care, e.g. nitrendipin 10 mg 1-0-1, amlodipine 5mg 1-0-0 or doxazosin 2 mg 1-0-1)

Maintenance dose: Uptitration to normotension

Route of administration: p.o.

Duration: Through recovery, unless discontinuation is necessary for clinical reasons

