### 8.1.9 Procedures to assess subjects compliance

For "antiviral" treatment arms and sub-studies only hospitalized patients will be included and intake of peroral medication will be controlled. In sub-study C all substances will be administered intravenously, therefore therapy adherence will not be an issue. In substudy B, in case of a discharge, patients will receive the required medication for the full treatment course.

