### 8.5.2 Screening investigation

During the screening procedure the patients' eligibility for each trial arm will be checked. The main prerequisite is a laboratory or radiologically proven infection with SARS-CoV-2. After obtaining informed consent the following procedures will be performed:

Vital parameters will be checked (body temperature, blood pressure, heart rate and respiratory rate). An ECG will be written, with special focus on the QTc time (recent ECGs may be used alternatively). For all patients a baseline laboratory analysis is required including differential blood counts, coagulation including D-dimer, electrolytes kidney function parameters (creatinine, blood urea nitrogen), liver function parameters (AST, ALT, total bilirubin), uric acid, blood glucose levels, lactate dehydrogenase levels, creatinine kinase, troponin T, C-reactive protein levels, IL-6, HBsAg, HIV antigen. Alternatively, to avoid blood loss, blood parameters obtained within 24h hours earlier can be used instead. Medical history, allergies and intolerances, and the disease course (first symptoms, etc.) will be documented. A physical examination will be performed. A pregnancy test will be done during the screening visit, and thereafter at least once a month in females with childbearing potential. Noteworthy, most of these procedures are part of normal clinical routine.

If the patient is eligible for study participation, he or she will be randomized in the next step.

Sub-study B: In- and outpatients may be included. For inpatients, blood sampling will be performed as part of their normal routine (3x/week). For outpatients and for patients discharged from hospital early, visits at the home of patients will be organized by the study staff, until the disease has dissolved (>48h no symptoms). For control groups a total of 4 blood samples will be drawn (Baseline and 3x a week, for a week). The visits at home will be specifically planned in order not to break home quarantine of these patients. Study staff will be wearing the required protection during these visits and will not include a risk population.

Healthy volunteers will be included as another control group.

Blood sampling for genetic analyses will be performed during screening, if the separate informed consent form is signed.

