#### ADJUNCTIVE THERAPIES

Randomization to one of the adjunctive therapies is desirable but not necessary. To make it more feasible, it is recommended that eligibility for adjunctive therapies is discussed during daily ward rounds.

For sub-study A patients who are not on chronic oral anticoagulation are eligible.

For sub-study B only hypertensive patients (>130/85mmHg) are eligible. Those patients with established arterial hypertension and antihypertensive treatment will be randomly switched to non-RAS-blocking therapy (e.g. nitrendipine or doxazosin, depending on comorbidities and concomitant medication) versus "stay-on-any-RAS-blockade". Patients with previously undiagnosed arterial hypertension will receive candesartan, as RAS blocking agent, and a non-RAS-blocking agent as standard of care (e.g. nitrendipine, amlodipine or doxazosin, depending on comorbidities and concomitant medication). Treating physicians will titrate the dose to normotension and may add other non-RAS blocking therapy if the maximum dose of the chosen antihypertensive medication does not suffice. RAS-fingerprint will be measured at the same timepoints. In case of an early discharge, RAS fingerprint will be measured at least once weekly (i.e. on days 7±1, 14±1, 21±1, 28±1, through recovery).

Additional analysis of local RAS activity in the lung will be performed in bronchoalveolar lavage samples in case of clinically indicated bronchoscopy or lung tissue following autopsy. End-of study visit will be performed after full recovery.

For asunercept the treatment will be administered once per week intravenously up to four weeks, or until hospital discharge or death, whichever occurs first. The clinical endpoints (including WHO ordinal scale,

NEW Score, oxygenation, etc.) will be obtained on a daily basis during visitation or until death or hospital discharge. Blood pressure, heart rate, respiratory rate, oxygen demand, oxygen saturation, mode of oxygen delivery, concomitant medication and radiologic changes regarding CXR/CT/lung ultrasound are documented as part of routine care. Laboratory analyses (similar to screening investigation) including c-reactive protein, D-Dimer, IL-6 and troponin levels will be performed three times a week, and in case of clinical necessity possibly more often.

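### Section 7.1.4 of the Protocol treats one screening pregnancy test as enough because participation stops at day 29, which is untrue for sub-study B and conflicts with the monthly testing rule

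*Protocol*

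**What the plan says.** Section 7.1.4 lets women of childbearing potential enrol after a negative screening test and adds that, while the trial lasts, "negative pregnancy tests are required at least once a month". It then says that after the day-29 evaluation "the study ends for each participating patient", and concludes "Thus, a pregnancy test during the screening visit should be sufficient". Women of childbearing potential are kept out of the asunercept part only.

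Other sections describe sub-study B differently:

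- Section 7.1.5 applies the day-29 end to the antiviral arms and continues: "The study ends after full recovery (or death) for patients in sub-studies B and C". Section 8.5.4 says the same.
- Section 8.1.1, for sub-study B: "Duration: Through recovery, unless discontinuation is necessary for clinical reasons".
- Section 8.1.9: "In substudy B, in case of a discharge, patients will receive the required medication for the full treatment course".
- Section 8.5.3, on sub-study B: "End-of study visit will be performed after full recovery".
- Section 8.5.2 requires the screening test "and thereafter at least once a month in females with childbearing potential", with no exception.

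The pregnancy-test row of Table 1 has an entry at screening and another at follow-up that applies only where feasible. It has none during treatment. Section 10.1 gives day 29 as the end of study for the individual patient without excepting sub-studies B and C.

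**The concern.** A safety rule rests on a statement that the protocol contradicts in the very next section. Once that statement fails for sub-study B, nothing else in section 7.1.4 supports dropping the repeat tests.

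The sub-study is open to these women and also takes outpatients, and its drug is supplied for use at home after discharge. A site that follows section 7.1.4 and Table 1 could keep a woman on candesartan or a comparator past day 29 with no further test. A site that follows section 8.5.2 would test her monthly. The protocol does not say which section takes precedence.

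Pregnancy is an exclusion under section 7.1.3, and section 9.2.4 requires any pregnancy to be reported to the sponsor immediately. The candesartan contraindications listed in section 9.1.1.5 do not mention pregnancy, so the general exclusion and the testing rule carry that protection. The matter is one of participant safety and consistent conduct across sites. It has no bearing on the statistical properties of the trial.

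**Working it through.** The protocol gives no figure to reproduce here. The check compares the sections and then counts the tests each rule requires.

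**Step 1: does the reason hold for each part of the trial?**

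| Part | When participation or treatment ends | Day-29 reason |
|---|---|---|
| Antiviral arms | Participation ends at day 29 (7.1.5, 8.5.4) | Holds |
| Sub-study B | Treatment until recovery (8.1.1); participation until recovery or death (7.1.5, 8.5.4) | Fails |
| Sub-study C, asunercept | Participation until recovery or death (7.1.5) | Fails, but these women are excluded (7.1.3, 7.1.4) |
| Sub-study C, Pentaglobin | Participation until recovery or death (7.1.5); treatment for 5 days (8.1.1) | Fails for study end, but treatment is over well before day 29 |

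The practical effect therefore falls on sub-study B.

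**Step 2: how many repeat tests does each rule require?**

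The monthly rule is taken from sections 7.1.4 and 8.5.2. A month is taken as 30 days (my assumption). Repeat tests due after screening = floor(days ÷ 30).

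- Antiviral arms, 29 days: floor(29 ÷ 30) = 0. The monthly rule and the screening-only conclusion agree.
- Sub-study B, with treatment lengths assumed for illustration because the protocol sets no maximum:

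| Days on treatment | Monthly rule (8.5.2) | Screening only (7.1.4) |
|---|---|---|
| 45 | floor(45 ÷ 30) = 1 | 0 |
| 60 | floor(60 ÷ 30) = 2 | 0 |
| 90 | floor(90 ÷ 30) = 3 | 0 |

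The two rules agree up to day 29 and diverge from day 30.

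**Step 3: do the other safeguards cover the gap?**

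- Willingness to use contraception (7.1.2) is not a test.
- The follow-up test in Table 1 applies only where feasible, and in sub-study B follow-up comes after recovery.
- When the end-of-study contact is by telephone (8.5.4), a question about pregnancy or the last menstrual period can stand in for a test. In sub-study B that contact also comes at recovery.

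None of these provides a test while randomised treatment continues. Only the monthly rule does, and that is the rule section 7.1.4 appears to set aside.

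**The case against.** The strongest reply is that section 7.1.4 states the monthly rule first and then merely explains why no repeat falls due for someone who finishes at day 29. On that reading the explanation does not reach a woman still in sub-study B, section 8.5.2 continues to govern, and the fault is one loose sentence. For the antiviral arms this is right, as the count in step 2 shows. For sub-study B it is a possible reading but not a safe one. The sentence names every participant, Table 1 schedules tests in line with the screening-only conclusion, and a site has no stated reason to prefer section 8.5.2.

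A second reply is that few women would reach the gap. Table 1 heads the treatment period as 28 days, and section 8.5.2 stops home visits once a patient has been symptom-free for more than 48 hours. Sub-study B aims for 100 patients with raised blood pressure or treated hypertension, and section 8.2 expects hospitalised patients to be older. The point about small numbers stands. The 28-day heading does not settle the matter, because the sub-study B column beneath it runs to recovery.

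A third reply is that section 10.1 goes on to provide regular check-ups, for example weekly, when disease is still ongoing. It does, so these patients are not forgotten, but the check-ups include no pregnancy test. The provision also shows that the protocol expects some patients to be unrecovered at day 29.

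**Conclusion.** The concern holds. The stated reason for treating a screening test as enough is false for sub-study B, and the conclusion conflicts with the monthly rule both within section 7.1.4 and in section 8.5.2. The difference is at least one omitted test for any woman of childbearing potential treated for 30 days or more: 1, 2 or 3 tests at 45, 60 or 90 days against 0. Those counts assume a 30-day month and illustrative treatment lengths. How many women would be treated that long cannot be derived from the protocol, and the number may be small.

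For sub-study C only the stated end of participation is wrong. Sample size, error rates and the primary analysis do not change. The correction should be made because it concerns safety during randomised treatment and the text supports two opposite practices.

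**What to change.** 1. In section 7.1.4, restrict the last two sentences of the first paragraph to patients whose participation ends at day 29.
2. Add that women of childbearing potential in sub-study B are tested at least monthly until randomised treatment ends, as section 8.5.2 already requires.
3. In Table 1, add the monthly test to the sub-study B treatment column of the pregnancy-test row.
4. In section 10.1, except sub-studies B and C from the day-29 end of study, in line with sections 7.1.5 and 8.5.4.

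The cost is one paragraph, one table row and one sentence. No procedure is added beyond section 8.5.2. For discharged patients the test can be done at the weekly sampling that section 8.5.3 already plans.

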### 7.1.5 Study duration

The clinical status of all patients will be evaluated on day 29. Thereafter, the trial ends for the individual patient randomized to antiviral treatment arms. The study ends after full recovery (or death) for patients in sub-studies B and C.

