| 14 REFERENCES                                                       | 83 |

Table 1 VISIT AND ASSESSMENT SCHEDULE

| PERIODS                          | Name     | SCREENING |               | TREATMENT          |                    |                                                                                             |                   |                    | FOLLOW-UP Treatment arms 1-4               | Follow-up substudies                       |
|----------------------------------|----------|-----------|---------------|--------------------|--------------------|---------------------------------------------------------------------------------------------|-------------------|--------------------|--------------------------------------------|--------------------------------------------|
|                                  | Duration |           |               | 28 days            |                    |                                                                                             |                   |                    | Day 29                                     | Up to 7 days after recovery                |
| VISITS                           | Number   | 1         | 2             | 3                  | 3 A                | 3 B                                                                                         | 3 C               | 4                  | 4                                          | 4                                          |
|                                  | Name     | Screening | Randomization | Treatment arms 1-4 | Substudy A         | Sub-study B                                                                                 | Sub-study C       | All treatment arms | Follow-up (Telephone call/inpatient visit) | Follow-up (Telephone call/inpatient visit) |
|                                  | Time     |           |               | Day 1-7, or longer | Days 1 - discharge | Days 1 - recovery                                                                           | Days 1 - recovery | Day 1-29           | Day 29 (±7)                                |                                            |

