- Sub-study B: To investigate clinical outcomes (blood pressure, dyspnea, body temperature, patient-reported fear/anxiety) and the RAS-fingerprint of patients with SARS-CoV-2 infection and arterial hypertension randomized to RAS blocking (“stay-on-any-RAS-blockade” for those patients with previously treated hypertension; candesartan for those with blood pressure  $\geq 140/90$ , measured twice after SARS-CoV-2 infection) versus non-RAS blocking treatment (nitrendipine or doxazosin).
- Sub-study C: modified SOFA score,  $paO_2/FiO_2$  ratio, or  $SpO_2/FiO_2$  ratio
- Pharmacokinetics of antiviral substances, if assays are available (e.g. trough level analysis of lopinavir/ritonavir)
- Sub-Study C for Pentaglobin: CRP, PCT, IL-6, differential blood count (baseline and day 2, 3, 7), IgM, IgA and IgG-levels (baseline, day 2, 3, 4, 5), modified SOFA score (baseline, on day 7 and day 28 of study participation)

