#### 8.5.4 End-of-study (EOS) examination

For all patients except for sub-study B and, in part, C the study will end on study day 29, although also day 60 and 90 mortality will be assessed. Either a telephone call or, if the patients are still hospitalized, an EOS visit will be performed. Given the specific circumstances, a formal visit at a hospital will not be required for each patient and only be performed for specific circumstances (e.g. ongoing, relevant side effects). Otherwise the telephone call will be the EOS. For sub-study B or C the study will end with patient death or full recovery. In case a telephone call is the EOS, females with childbearing potential will be asked about possible pregnancies, asked to do a pregnancy test or asked about the date of their last menstruation.

For control groups the last blood sample/oral/nasopharyngeal swab will be the EOS.

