## 10 FOLLOW-UP

### 10.1 Follow-up of study participants including follow-up of adverse events

The study will end for the individual patient on day 29. However, in case of ongoing SARS-CoV-2 disease or ongoing side effects regular check-ups (e.g. once a week) will be performed to follow-up on the outcome. Importantly, given the special circumstances these follow-ups will be performed by telephone calls, if possible.

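### The protocol contradicts itself on when follow-up ends in sub-studies B and C; under its recovery-based rule, SAE incidence would be counted over a shorter time in the faster-recovering arm

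*Protocol*

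**What the plan says.** Several parts of the protocol define the end of follow-up for sub-studies B and C, and they differ.

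Recovery-based rules:
- Section 7.1.5: "The study ends after full recovery (or death) for patients in sub-studies B and C".
- Section 8.5.4: "For sub-study B or C the study will end with patient death or full recovery". The same section opens by excepting sub-study B and part of C from the day-29 end of study, without saying which part.
- Table 1, sub-study follow-up column: "Up to 7 days after recovery". The main treatment arms have day 29 in the matching cell.
- Section 8.5.2: home visits in sub-study B run until symptoms have been absent for more than 48 hours.
- Section 8.5.3, adjunctive therapies: the sub-study B end visit follows full recovery, and asunercept clinical scoring "will be obtained on a daily basis during visitation or until death or hospital discharge".

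Day-29 rules:
- Section 7.1.5, first sentence: "The clinical status of all patients will be evaluated on day 29".
- Section 7.1.4: "after evaluation of day 29 status (hospitalization, clinical performance etc.) the study ends for each participating patient".
- Section 10.1: "The study will end for the individual patient on day 29".

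The outcomes concerned are mortality at days 15, 29, 60 and 90, cumulative SAE incidence (section 11.6.3, no window stated), oxygen- and ventilator-free days to day 29, and for Pentaglobin the "modified SOFA score (baseline, on day 7 and day 28 of study participation". Section 11.5 rules out imputation.

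**The concern.** A site cannot tell from this text whether a sub-study patient who recovers on day 10 is still followed to day 29, or whether vital status at days 60 and 90 is collected. Patients may join a sub-study without joining the main study (sections 5.1, 7 and 7.1.1), so main-study contacts do not always fill the gap.

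Under the recovery rule, the length of observation is set by the outcome that treatment is meant to change. A cumulative incidence without a fixed window then counts events over unequal time in the two arms. This matters most for the asunercept safety comparison, where weekly dosing may run for up to 4 weeks. The data would also be uneven for endpoints tied to a fixed day, such as Pentaglobin mSOFA on day 28.

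**Working it through.** **1. Where the texts meet.** Take a sub-study-only patient who recovers on day 10.
- Sections 7.1.5 (last sentence) and 8.5.4: study over on day 10.
- Table 1: over by day 17 (10 + 7).
- Section 7.1.5 (first sentence) and sections 7.1.4 and 10.1: day 29.
- Days 60 and 90: section 8.5.4 mentions this mortality in the sentence that excepts B and part of C. Whether the exception covers the mortality check or only the day-29 end cannot be decided from the wording. Section 7.1.6 provides the check explicitly for withdrawn patients; no equally explicit provision covers those who recover and complete.

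**2. Rates used for illustration.** The protocol gives no recovery or SAE rate for B or C. I borrow the main-study rates in section 11.2: 0.069 and 0.043 per day, from medians of 10 and 16 days (ln 2/10 = 0.0693; ln 2/16 = 0.0433; ratio 1.6). As a check that these are read correctly, 154 events and a hazard ratio of 1.6 give power Φ(√(154/4) × ln 1.6 − 1.96) = 83.05%, against the stated 83.15%.

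**3. Mean observed time to day 29.** With g further days after recovery, capped at day 29, and deaths ignored: g + (1 − exp(−λ(29 − g)))/λ.
- g = 0: (1 − exp(−2.001))/0.069 = 12.5 days; (1 − exp(−1.247))/0.043 = 16.6 days; ratio 0.76.
- g = 7: 7 + (1 − exp(−1.518))/0.069 = 18.3 days; 7 + (1 − exp(−0.946))/0.043 = 21.2 days; ratio 0.86.

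**4. Apparent SAE incidence.** Assume the same constant SAE hazard h in both arms, before and after recovery. Observed incidence = 1 − [λ/(λ+h) × exp(−hg) × (1 − exp(−(λ+h)(29−g))) + exp(−λ(29−g)) × exp(−29h)]. With follow-up to day 29 for everyone it is 1 − exp(−29h) in both arms.

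| h per day | Full 29 days, both arms | g = 0, fast vs slow | Risk ratio | g = 7, fast vs slow | Risk ratio |
|---|---|---|---|---|---|
| 0.005 | 13.5% | 6.0% vs 7.8% | 0.76 | 8.7% vs 10.0% | 0.87 |
| 0.01 | 25.2% | 11.4% vs 14.8% | 0.77 | 16.5% vs 18.9% | 0.87 |
| 0.02 | 44.0% | 20.8% vs 26.6% | 0.78 | 29.8% vs 33.8% | 0.88 |

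**5. Mortality.** Assume true day-29 mortality of 10% in both arms. By day 29, 1 − exp(−29λ) = 86.5% and 71.3% of survivors have recovered.
- If their vital status is missing and they are dropped, observed mortality is 0.10/(0.10 + 0.90 × 0.135) = 45% in the faster arm and 0.10/(0.10 + 0.90 × 0.287) = 28% in the slower one. This is a bias against the faster arm.
- If they are counted as alive and 1% to 3% die later, missed deaths are 0.90 × 0.865 × (0.01 to 0.03) = 0.8 to 2.3 points and 0.90 × 0.713 × (0.01 to 0.03) = 0.6 to 1.9 points. The faster arm gains only 0.1 to 0.4 points.

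**6. Pentaglobin day-28 mSOFA.** An earlier exit would leave it missing. Nothing in the protocol fixes the direction of the resulting bias.

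**The case against.** A reader might infer that a patient who recovers early is owed no later assessment at all. The documents do not support that. Section 7.1.5 first has day-29 status evaluated for all patients, then ends the trial for the antiviral arms, then turns to B and C. Read in order, B and C may continue past day 29 rather than stop before it. Table 1 places the WHO scale and NEWS under all treatment arms for days 1 to 29, and sections 8.5.3 and 11.6.1 provide contact on days 11 and 29 after early discharge. Loss of day-15 or day-29 mortality is therefore not established. Nor is day-60/90 mortality clearly excluded: the objectives list it without a sub-study limit.

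This stands as a limit on the claim but does not settle the matter. The day-11/29 calls sit with the antiviral arms, and section 11 says it outlines the main part. Table 1 replaces day 29 with a recovery-based contact for the sub-studies, and the sub-study B home visits stop once symptoms are gone.

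A reader might also infer that every fixed-day endpoint is biased in favour of the faster arm. Only the SAE direction is shown; mortality can go either way.

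The size is open to challenge too. The borrowed rates describe a one-category improvement, which generally comes before full recovery, so early exit is probably overstated. Secondary analyses are exploratory, and an SAE window may be set in the separate sub-study SAPs. But an analysis plan cannot supply data that sites were told to stop collecting.

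**Conclusion.** The concern holds as a contradiction that must be reconciled, with a conditional bias. The protocol gives incompatible ends of follow-up for B and C (recovery or death, up to 7 days after recovery, day 29) and leaves day-60/90 vital status unclear for these patients.

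If the recovery rule is followed, SAE incidence favours the faster-recovering arm even when true hazards are equal. The apparent risk ratio is about 0.76 to 0.78, or about 0.87 to 0.88 with the 7 days in Table 1. These figures rest on main-study improvement rates used as recovery rates, an assumed constant SAE hazard of 0.005 to 0.02 per day, and no deaths. They show direction and rough order, not an estimate for B or C. The point concerns safety and secondary endpoints; no damage to the main-study primary endpoint is shown.

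**What to change.** Reconcile sections 7.1.4, 7.1.5, 8.5.3 (adjunctive therapies), 8.5.4 and 10.1 with Table 1, so that one rule applies to every randomised COVID-19 patient in B and C, recovered or not and discharged or not:
- from that sub-study's randomisation to day 29: SAEs, WHO scale, and oxygen and ventilation status;
- vital status on days 60 and 90;
- recovery-based follow-up only as an addition beyond day 29.

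State in section 11.6.3 that SAE incidence is counted to day 29. The telephone, register and chart routes already in sections 7.1.6, 8.5.3 and 8.5.4 are enough. The two control groups of sub-study B without COVID-19 are not affected.

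The cost is protocol wording, plus a day-29 call and day-60/90 vital-status checks for patients who are in a sub-study only.
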